### Sample size

Sample size calculation has been based on the results of an observational study conducted in our Rehabilitation Institute in a sample of 179 patients. They were over 65 years old, medium-high fall risk profile, consecutively discharged from January to June 2013 and with a 6-month fall rate of 22.2%.

Consequently, we have estimated that 290 patients (145 in each group) are needed to detect a reduction of 40% of fallers in the intervention group with respect to the control one, with a power (1-beta) of 80%, alpha of 0.05 and an expected dropout rate of about 6%.

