### Outcome measures

The primary outcome will be the proportion of fallers in the 6-month period after randomization. The secondary falls outcomes are the time between the first fall and the recurrent falls during follow-up and the percentage of patients sustaining two or more falls. A fall will be defined as “an event which results in a person coming to rest inadvertently on the ground or other lower level “ [24].

Other secondary outcomes include: changes in functional status (ADL, IADL and Barthel index), gait and balance measures (TUG or BEST test) and quality of life (EQ-5D).

The economic evaluations will be a combination of a cost-effectiveness and a cost-utility analysis [25] see list; we anticipated references [26]. The primary outcome measure for the cost-effectiveness analysis will be the percentage of people sustaining a fall during the 6-month follow-up. Within the cost-utility analysis the effects will be measured in terms of generic health-related quality of life descriptions, measured according to the standard Italian version of the EQ-5D [26], a self-administered questionnaire administered at baseline and after 6 months.

All healthcare and patient costs will be measured by means of a cost diary [27], in which participants continuously will record volumes of healthcare utilization during the 6 month follow-up period. In monthly telephone interviews, participants will be asked whether they had received care (or devices or services) or not. If participants will answer the question on a particular topic affirmatively, they will be asked to indicate the number of visits or details about the specific type of healthcare utilization. Data management will be organized “in-house”. Feasibility of the intervention program will be evaluated assessing participants compliance with the intervention protocol.

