## Discussion

The main strengths of this study are the target population and the administration of the prevention program.

Despite evidence of the effectiveness of falls prevention activities for community-dwelling older people, the applicability of these interventions has not, to date, been specifically evaluated in elderly population affected by multiple comorbidity, discharged from a multispecialistic rehabilitation medical setting. The inclusion of patients with mild-moderate cognitive impairment represents a further originality. In fact, most studies conducted in community-dwelling patients have not specifically addressed older adults with cognitive impairment, and the effectiveness of fall prevention interventions in this population is not known [9]. Elderly adults with cognitive problems are one of the most vulnerable sectors of our society with clear mental, social, and physical disadvantages. They are more likely to experience falls, and experience further mobility decline due to having fallen; therefore it is urgent to identify evidence based interventions for reducing the risk of falls and related injuries in people with cognitive impairment.

Finally, an additional strength of the study is the administration of a fall prevention program supported by the new home-based technologies. This may contribute to a new approach to prevent and treat fall risk in this population. To date, no adequately powered studies have investigated the effect of the Information and Communication Technologies (ICT) in a home fall prevention program. We aim the program will be feasible in terms of intensity and characteristics, but particularly in terms of patient and provider compliance, which represent a possible barrier in successful implementation of fall prevention strategies [9].

Furthermore, the results of the economic evaluation could provide information about the cost-effectiveness of the intervention and the effects on quality of life. In case of shown effectiveness and cost effectiveness, the program could be implemented into health services settings.

All results from the study will be communicated by publication without any restriction.

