### Limitation

The main potential critical aspect of our study is the sample size calculation. Epidemiological data on prevalence and fall rate incidence of subjects with a high fall risk profile coming from a multispecialistic rehabilitation setting are lacking. Consequently, we powered the study on the fall rate observed in a small number of patients discharged from our Institute that we hope will be confirmed in the usual care group.

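### The planned 290 patients (145 per group) give about 48–51% power, not 80%: the stated inputs require 290 evaluable patients in each group

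*Protocol article*

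**What the plan says.** The Outcome measures section fixes a binary primary endpoint: "The primary outcome will be the proportion of fallers in the 6-month period after randomization". The Data analysis section compares it between groups by chi-square, with alpha 0.05 for all analyses, and Study design and randomization gives 1:1 allocation.

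The Sample size section takes its event rate from 179 patients of the same institute, "consecutively discharged from January to June 2013 and with a 6-month fall rate of 22.2"%. It then states that "we have estimated that 290 patients (145 in each group) are needed to detect a reduction of 40% of fallers in the intervention group", with 80% power, alpha 0.05 and a dropout of about 6%.

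The Limitation section says "The main potential critical aspect of our study is the sample size calculation". Its reason is that the event rate comes from few patients: "we powered the study on the fall rate observed in a small number of patients discharged from our Institute that we hope will be confirmed". The arm meant there is usual care. Progress of the study reports that recruitment closed with 290 patients in total.

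**The concern.** All the inputs to the calculation are in the text, so the result can be reproduced, and it cannot be made to equal 145 per group. The formula that matches the planned test gives 290 for one group before any dropout allowance, whereas the protocol reports 290 as the whole trial with dropout included.

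What is at stake is how the primary result is read. At the effect the trial was designed to find, the chance of a significant result is about one in two. The Discussion makes implementation conditional on shown effectiveness, so a null result could be taken as evidence that the programme does not work, when the trial had little ability to tell.

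**Working it through.** **Inputs**

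- Control proportion p1 = 0.222 (Sample size). The Limitation section confirms that this is the rate expected under usual care.
- Effect: a 40% reduction relative to control (Sample size). It must be relative, since 22.2% cannot fall by 40 percentage points. So p2 = 0.222 × 0.60 = 0.1332 and the difference is d = 0.0888.
- Power 80%, so z = 0.8416. Alpha 0.05; sidedness is not stated. Two-sided is assumed because the planned test is a chi-square, so z = 1.9600. One-sided is shown below.
- 1:1 allocation; 6% dropout.

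**Step 1: trying to reproduce the protocol's figure**

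n per group = [1.9600 × √(2p̄(1 − p̄)) + 0.8416 × √(p1(1 − p1) + p2(1 − p2))]² / d², with p̄ = (0.222 + 0.1332)/2 = 0.1776.

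- √(2 × 0.1776 × 0.8224) = √0.29212 = 0.54048
- √(0.172716 + 0.115458) = √0.28817 = 0.53682
- Numerator: (1.0593 + 0.4518)² = 2.2835
- Denominator: 0.0888² = 0.0078854
- n = 289.6, rounded up to **290 per group**, 580 in total
- With dropout: 290/0.94 = 308.5, rounded up to **309 per group**, 618 in total

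The number 290 does appear, but as the evaluable size of one group.

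**Step 2: other standard methods**

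| Method (80% power, 22.2% vs 13.32%) | Per group, evaluable | Per group, with 6% dropout |
|---|---|---|
| Two-sided, pooled variance | 290 | 309 |
| Two-sided, unpooled | 287 | 306 |
| Two-sided, arcsine | 287 | 305 |
| Two-sided, continuity-corrected | 312 | 332 |
| One-sided, pooled | 228 | 243 |
| One-sided, unpooled | 226 | 241 |
| One-sided, continuity-corrected | 250 | 266 |

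None comes near 145.

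**Step 3: power of the trial as sized**

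Power = Φ[(d√n − 1.9600 × 0.54048)/0.53682]. After 6% dropout, 145 × 0.94 = 136.3, taken as 136.

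- n = 145: (1.0693 − 1.0593)/0.53682 = 0.019, power **50.7%**
- n = 136: (1.0356 − 1.0593)/0.53682 = −0.044, power **48.2%**
- Exact enumeration of the chi-square test: 51.3% and 48.8%
- One-sided, same formula with 1.6449: 63.2% and 60.8%

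**Step 4: what the trial can detect**

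Solving the Step 1 formula for p2 at 80% power, two-sided:

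- n = 136: p2 = 0.098, a relative reduction of about 56%
- n = 145: p2 = 0.101, a relative reduction of about 54%

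**Step 5: what happens if the target effect is observed**

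The nearest whole counts are 30/136 (22.1%) and 18/136 (13.2%). The uncorrected chi-square is 3.64, p = 0.056. A trial that observed its own design effect would narrowly miss significance.

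**The case against.** The best attempt to rescue the figure takes 22.2% as the intervention rate, so that the control rate is 0.222/0.60 = 37%. The same formula then gives 149 per group, close to 145. But the Limitation section assigns the observed rate to usual care, and this reading still needs 159 per group after dropout.

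Several qualifications are fair:

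- Sidedness is not stated, so 48–51% rests on an assumption. The one-sided range of 61–63% still falls well short of 80%.
- The exact match at 290 suggests that a per-group number was reported as the total, but the protocol does not say how 290 was obtained. This is an inference, and the shortfall does not depend on it.
- The Limitation section does warn readers about the sample size. Its worry is that the fall rate may differ from 22.2%. The deficit here is present when that rate is exactly confirmed, so the warning does not cover it.
- The sentence "To date, no adequately powered studies have investigated the effect" in the Abstract and Discussion describes earlier research. At most it implies that this trial fills the gap. The explicit power claim stands only in the Sample size section.
- An article may leave reporting details to a fuller document. That covers omissions. It does not cover a stated number that conflicts with its own inputs.

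**Conclusion.** The concern holds, and the correction should be treated as essential. Under the protocol's own inputs, 290 patients in total do not give 80% power for a 40% relative reduction from 22.2%. The requirement is 290 evaluable or 309 randomised per group, so the trial has slightly under half the 618 patients it needed (290/618 = 47%). Two-sided power is about 48% with the planned dropout and 51% without.

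This rests on 22.2% being the control rate, 40% being a relative reduction, and a two-sided test. The first is stated in the protocol, the second is the only possible reading, and relaxing the third does not bring power to 80%.

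**What to change.** Recruitment has closed and no further enrolment is proposed. The changes are to text, and should be made before the results are known:

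1. **Sample size.** State that 290 randomised, about 272 evaluable, gives about 48% power (two-sided) for 22.2% against 13.3%, and 80% power only for a relative reduction of about 56% (to 9.8%). State that 80% power at a 40% reduction would have needed 290 evaluable, or 309 randomised, per group. State the sidedness of alpha.
2. **Limitation.** Name the calculation error separately from the uncertainty in the fall rate.
3. **Interpretation.** Commit to reporting the risk difference and risk ratio with 95% confidence intervals, and to calling a non-significant primary result inconclusive and not evidence of no effect.
4. **Abstract and Discussion.** Reword the sentence on adequately powered studies so that it does not suggest this trial is one. This is the least important of the four.

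The cost is a few sentences and a less favourable stated power.

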### Data analysis

Data will be primarily analyzed according to the intention-to-treat principle.

An on-treatment analysis will be subsequently performed to assess whether protocol deviations have caused bias. Participants with documented deviation from the study protocol (i.e. patients in the intervention group who did not receive the entire intervention or participants in both groups with incomplete follow-up data) will be excluded from this analysis. Chi-square analysis will be used to compare the proportion of fallers and non-fallers between groups. Cox proportional hazards regression will be conducted with time to first fall within 6 months of follow-up as outcome measure with age, sex, anthropometric data, prevalent disease, comorbidities, residual disability, marital status, social and economic status, MMSE and baseline variables as covariates. Multiple linear regression analyses will be used to compare differences in the other secondary outcomes at 6 months follow-up between groups. ANOVA with repeated measures will be used to analyze differences between groups from baseline to follow-up. Differences in baseline characteristics between groups will be examined using parametric (*T*-test) and non-parametric (Chi-square) tests. No ad interim analysis will be performed.

The economic evaluations will be conducted from a societal perspective and involve calculating cost-effectiveness ratio. The incremental costs and effects of the intervention will be compared with control group. The alfa level for all analyses is set at 0.05. Statistical analyses will be performed using STATA 13 program.

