## Background

About one-third of people over the age of 65 fall at least once a year [1]. Moreover people who have fallen are at higher risk of falling again [2] and show an increase in morbidity, mortality and healthcare utilization [2], which implies an increase in healthcare costs [3–5].

These facts emphasize the need to adopt measures to prevent falling in older persons.

Several fall prevention strategies including educational support, physical exercise and modification of environmental factors have been evaluated in studies [1] conducted in elderly people living in community.

In general, evidence suggests that interventions individually tailored to target risk factors seem to be more effective than those applied as a standard package [6].

Nevertheless, a systematic Cochrane reviewed 159 randomized trials involving 79,193 older persons living in community, failed to establish which fall prevention interventions are more effective, but confirmed the positive effect of the intervention in persons with history of falling or in those at higher risk [7].

However, it should be emphasized that even when programs for fall prevention have been successful in a controlled research setting, the transfer of similar protocols to real world settings has not always resulted in fall prevention [8]. Both patient and provider compliance with the protocol, as well as expertise in delivering services, such balance training, are felt to be possible barriers for a successful implementation [9].

In this scenario the role of Information and Communication Technologies (ICT) in a home fall prevention program could be crucial. Telephone support, telemonitoring and tele-exercise program could improve patient’s compliance, as well as lead to a personalized management of the patient’s risk profile allowing the identification of a well-defined model, e.g. a home fall prevention program.

The role of ICT in a home fall prevention program has never been explored and besides this, studies focusing on economic evaluations in the context of a multidisciplinary intervention program are lacking [10–14].

This article describes the design of a randomized controlled trial aiming at evaluating the efficacy of a multidisciplinary intervention program, based on a tele-health home treatment, in elderly patients with high risk of falling discharged from a rehabilitation medical setting and living in community.

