## Measurements

### Baseline assessment

Fall risk stratification will be performed in all potentially eligible patients using a Berg Balance Scale [18]. We will consider at medium-high risk of falls patients with a Berg Balance scale score ≤ 45 and/or at least one episode of fall within the last 12 months, as well as people presenting at least one fall episode undertaken during hospitalization in our Institute. Cognitive state will be evaluated using Mini Mental Test Examination (MMSE) [19].

In patients who have signed the informed consent, fear of falling, gait and balance problem, functional status and quality of life is assessed. Fear of falling will be measured by the Italian version of Falls Efficacy Scale (FES) [20], gait and balance by Timed Up and Go Test (TUG) [21] or Balance Evaluation System’s Test (BEST) in patients with Parkinson disease, functional state by Activities Daily Living scale (ADL), Barthel Index [22], Instrumental Activity Daily Living scale (IADL) [23] and quality of life by the EQ-5D questionnaire. Daily doses of drugs considered correlated with fall risk such as antihypertensive drugs, diuretics, beta-blocker, calcium antagonists, nitrates, antiarrhytmics, insulin, oral hypoglycemic drugs, neuroleptics, antidepressives, antiepileptic and dopaminergic and thyroid drugs will be also recorded.

The same operators previously involved in baseline evaluations will collect them at the end of 6-month follow-up as well.

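### The only test named for the primary proportion of fallers is an unadjusted chi-square; a short pre-specified covariate adjustment would give a modestly more precise estimate from data already collected

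*Protocol article*

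**What the plan says.** The Outcome measures section defines the endpoint: "The primary outcome will be the proportion of fallers in the 6-month period after randomization". The Data analysis section fixes its test: "Chi-square analysis will be used to compare the proportion of fallers and non-fallers between groups". No other method is named for that proportion.

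The same section then plans a Cox regression of time to first fall. Its covariates are age, sex, anthropometric data, prevalent disease, comorbidities, residual disability, marital status, social and economic status, MMSE and, without further naming, baseline variables.

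Several prognostic variables are known before allocation. Under Baseline assessment, "Fall risk stratification will be performed in all potentially eligible patients using a Berg Balance Scale". Fall history over 12 months and falls in hospital are the other two routes to eligibility, and MMSE and age are checked for eligibility. The Background states that "people who have fallen are at higher risk of falling again", and the Discussion says that older adults with cognitive problems fall more often.

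**The concern.** The protocol selects patients on Berg score and fall history because it regards them as markers of fall risk, then leaves both out of the comparison that decides the trial. A chi-square test can use no baseline information. If baseline variables predict falling among those randomised, part of the outcome variation that could be explained is counted as noise.

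The adjusted Cox model does not fill the gap. It estimates a hazard ratio for time to first fall, not a difference or ratio in the proportion of fallers. Its covariates are also not fixed, so the choice could still be made with the data in view.

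Recruitment has closed at 290 (Progress of the study), so more patients cannot supply the missing precision. The analysis is one of the few places where some can still be gained.

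**Working it through.** **Inputs.** All are from the Sample size section unless noted.
- Control proportion p1 = 0.222 ("with a 6-month fall rate of 22.2" per cent).
- Effect: "to detect a reduction of 40% of fallers in the intervention group with respect to the control one". Read as relative, since a 40-point fall from 22.2% is impossible: p2 = 0.6 × 0.222 = 0.1332, difference d = 0.0888.
- "with a power (1-beta) of 80%, alpha of 0.05 and an expected dropout rate of about 6" per cent.
- 145 per arm. Evaluable: 145 × 0.94 = 136.3, taken as 136.
- Sidedness is not given (Data analysis: "The alfa level for all analyses is set at 0.05"); two-sided is assumed.

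**The plan's own figure.** Mean proportion = 0.1776.
- A = √(2 × 0.1776 × 0.8224) = 0.5405
- B = √(0.222 × 0.778 + 0.1332 × 0.8668) = 0.5368
- n per arm = (1.960 A + 0.842 B)² / d² = 2.2835 / 0.007885 = 289.6, so 290 **per arm**, or 580 in total before dropout.

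The stated 290 in total is not reproduced. It equals the per-arm requirement, which is consistent with a per-arm/total mix-up, though that is an inference.

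**Unadjusted power.** Power = Φ[(d√n − 1.960 A) / B].
- n = 136: (1.0356 − 1.0593) / 0.5368 = −0.044, power 48.2%.
- n = 145 (no dropout): 50.7%.
- One-sided: 60.8% and 63.2%.

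**Power with adjustment.** If covariates explain a share R² of outcome variance, the effective n is about n / (1 − R²). The R² values are assumptions.

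| R² | Effective n per arm (from 136) | Power | Equivalent extra patients, 2 × 136 × [1/(1 − R²) − 1] |
|---|---|---|---|
| 0 | 136 | 48.2% | 0 |
| 0.05 | 143.2 | 50.2% | 14 |
| 0.10 | 151.1 | 52.4% | 30 |
| 0.15 | 160.0 | 54.7% | 48 |

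From 145 per arm the same three R² values give 52.8%, 55.0% and 57.4%.

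**Check by simulation.** Logistic model, one baseline risk score, 136 per arm, 4,000 trials per setting. The Monte Carlo standard error is about √(0.25/4000) = 0.8 points.

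| AUC of score | Chi-square | Adjusted logistic |
|---|---|---|
| 0.50 (no information) | 48.9% | 48.1% |
| 0.64 | 49.3% | 49.7% |
| 0.74 | 48.9% | 53.6% |
| 0.82 | 48.1% | 57.7% |

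The gain is near zero for a weak score and about 5 points for a moderate one. It reaches about 10 points only for a very strong one.

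**Can adjustment reach 80%?** That needs 136 / (1 − R²) = 290, so R² = 1 − 136/290 = 0.53, far above the range considered.

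**Fallers available to a model.** 136 × 0.222 + 136 × 0.1332 = 30.2 + 18.1, about 48. The Cox list has nine named items, several of them groups of variables, before the unnamed baseline variables. With study group that is at least ten terms, or at most 48/10 = 4.8 fallers per term. Study group plus four named covariates is five terms, or 48/5 = 9.6.

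**The case against.** The strongest reply is that nothing here is an error. An unadjusted chi-square test on a binary outcome is valid under 1:1 randomisation, matches a two-proportion sample size, and already allows for chance imbalance in its type I error. All of that stands. A reader might infer bias or an inflated false-positive rate; the documents support neither.

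A reader might also infer that no adjusted analysis of falls is planned. That is wrong: the Cox model follows in the next sentence, concerns the same event and gives an estimate with an interval. What remains is that it does not analyse the primary proportion and its covariates are not fixed.

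Nor can the predictors be called strong. The article gives no measure of predictive strength, and excluding low-risk patients narrows their range. Because the eligibility criteria are joined by and/or, Berg score and fall history still vary among those randomised, but how much they predict there is unknown.

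Two further inferences rest on silence and are not made here: that randomisation was unstratified, and that no confidence interval will be reported. A condensed article may leave both to the full protocol or analysis plan. A crude risk difference with an interval also follows from the 2×2 table without any model, so the economic evaluation does not depend on this change.

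**Conclusion.** The point holds as a low-cost improvement to a stated method. The primary proportion has no pre-specified covariate-adjusted estimate, although suitable covariates are on file for every participant. The cost is efficiency, not validity: about 2 to 7 points of power at 136 per arm if R² lies between 0.05 and 0.15, and possibly nothing if the covariates predict poorly.

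The size rests on three assumptions: a two-sided 5% test, the planned proportions of 22.2% and 13.3%, and the R² range. The simulation used a single risk score and tested the logistic coefficient, so it is only a guide to a four-covariate standardised analysis.

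It would be a mistake to read the 48% as a consequence of the chi-square test. It comes from the sample size, would remain close to 50% after this change, and needs its own correction.

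**What to change.** Before the data are analysed (the article places this after follow-up ends in June 2016), amend the Data analysis section:
- **Primary analysis:** logistic regression of faller status on study group, Berg score, a fall in the previous 12 months or in hospital (one indicator), age and MMSE. Standardise over the trial population to give the risk difference and risk ratio with 95% confidence intervals.
- **Sensitivity analysis:** the unadjusted chi-square test.
- **Covariates:** fix this list and the form of each covariate in advance, with no selection from the data.

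The Cox model can stay as a separate analysis of time to first fall.

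The cost is a change of wording; no new data are needed. The downside is slight added modelling with about 48 expected fallers, which is why the list should stay short. The sample-size statement should be corrected separately.

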**Fig. 1 Fig1:**
[figure not shown]
Design of the study

Each amendment to the protocol will be discussed with the Ethics Committee.

The fall risk profile will be assessed in all participants 7–10 days before the hospital discharge. Medium/high fall risk profile will be defined by a history of fall within the last 12 months and/or by a Berg Balance scale score ≤ 45, and/or patients with at least one fall event during in-hospital stay. Patients with a low-risk of recurrent of falling will be excluded from the RCT. After having signed the informed consent, participants in medium/high-risk group will be allocated into either the control or intervention group (1:1 allocation ratio) using a computer-generated random allocation sequence concealed from researches (http://www.randomization.com). Staff not involved in the study will undertake the sequence and concealment. People allocated to the control group will receive usual care, while people in the intervention group participate to the 6-month multifactorial falls prevention program. During the follow-up period the incidence of falls and volumes of health care utilization will be recorded in both groups.

Health staff will be unblinded to participant enrollment. All data will be managed and stored by an independent call center.

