### Progress of the study

Recruitment of eligible subjects started in April 2014 and ended in December 2015, resulting in a total of 290 patients enrolled in the trial. The follow-up will end in June 2016 and then data-analysis will be initiated.

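### The Cox model for time to first fall lists ten named covariates plus undefined baseline variables, more than about 50 expected first falls can support if that open term is read broadly

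*Protocol article*

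**What the plan says.** The Data analysis section tests the primary outcome, the proportion of fallers, with a chi-square test. It then specifies a Cox regression for time to first fall over 6 months, "with age, sex, anthropometric data, prevalent disease, comorbidities, residual disability, marital status, social and economic status, MMSE and baseline variables as covariates". It gives no selection step, penalisation or cap on the number of terms, and does not say what the last item of the list covers.

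The Baseline assessment section shows what that item could cover: Berg score, falls in the previous 12 months, in-hospital falls, six scales or tests of fear of falling, gait and balance, function and quality of life, and "Daily doses of drugs considered correlated with fall risk", for which 13 classes are listed.

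The number of events is not stated but follows from the Sample size section. That section takes a source cohort "with a 6-month fall rate of 22.2" per cent and a trial size "needed to detect a reduction of 40% of fallers in the intervention group with respect to the control one". The planned total is 290, and Progress of the study reports recruitment "resulting in a total of 290 patients enrolled in the trial".

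**The concern.** A Cox model is limited by the number of events, not the number of patients. With few events per parameter, the estimated treatment effect tends to move away from zero, its true variability grows, and the model-based standard error lags behind, so the confidence interval is too narrow. Several of the listed items also overlap: residual disability, ADL, Barthel and IADL all measure function.

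This is the only covariate-adjusted analysis of falls that the article names, and the only one of time to first fall. Its hazard ratio is therefore likely to be read beside the chi-square result. The undefined last item also leaves the covariate set to be settled later, possibly with outcome data in view.

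**Working it through.** **Inputs.** Control risk 0.222, 40% relative reduction, 290 patients, 80% power, alpha 0.05 and 6% dropout (Sample size); "1:1 allocation ratio" (Study design and randomization). Intervention risk: 0.222 x 0.6 = 0.1332. Implied hazard ratio under constant hazards: ln(1 - 0.1332) / ln(1 - 0.222) = 0.57, a log hazard ratio of -0.563.

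**The plan's own figure.** The plan gives no event count to reproduce. Its stated size, 145 per group, is not reproduced by the usual two-sided formula. With mean risk 0.1776, (1.96 x sqrt(2 x 0.1776 x 0.8224) + 0.842 x sqrt(0.222 x 0.778 + 0.1332 x 0.8668))^2 / 0.0888^2 gives 290 per group before dropout. That is a separate matter. It bears on this point only because 290 per group would yield 290 x 0.3552 = 103 first falls. The rest uses the 290 actually enrolled.

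**Expected first falls.** 145 x 0.222 + 145 x 0.1332 = 32.2 + 19.3 = 51.5. After 6% dropout: 51.5 x 0.94 = 48.4. With no treatment effect there would be about 60 to 64.

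**Parameters, at one per item.**
- Named items: age, sex, anthropometric data, prevalent disease, comorbidities, residual disability, marital, social and economic status, MMSE = 10. Events per parameter: 51.5 / 10 = 5.2, or 48.4 / 11 = 4.4 after dropout and counting study group.
- Adding nine baseline measures (Berg, previous fall, in-hospital fall, FES, TUG or BEST, ADL, Barthel, IADL, EQ-5D) and study group: 20. Events per parameter: 2.4 to 2.6.
- Adding 13 drug classes: 33. Events per parameter: 1.5 to 1.6.

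**Simulation.** 290 patients, 6% random censoring, 3,000 trials per setting, study group plus k covariates. Ranges run from independent, non-prognostic covariates to correlated, prognostic ones. At the planned effect (true log hazard ratio -0.563):

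| k | Mean estimate / truth | Empirical SD | Model SE / SD | 95% coverage |
|---|---|---|---|---|
| 0 | 1.02 | 0.295 | 1.01 | 95.9% |
| 9 | 1.04-1.05 | 0.312-0.313 | 0.97-0.99 | 94.8-95.2% |
| 19 | 1.09-1.10 | 0.329-0.350 | 0.92-0.95 | 93.0-94.5% |
| 32 | 1.16 | 0.370-0.381 | 0.89-0.90 | 92.5-92.6% |

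With no effect the mean estimate is close to zero throughout. Type I error is 4.1% (k = 0), 4.2-4.8% (9), 5.8-6.7% (19) and 7.5-7.7% (32). The Monte Carlo standard error of a 95% coverage figure is sqrt(0.95 x 0.05 / 3000) = 0.4 percentage points.

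**Comparison with a short model.** A second simulation fitted 5, 9, 19 and 32 covariates to the same data sets (3,000 trials; four covariates with log hazard ratios of 0, 0.3 or 0.5 per SD, the rest unrelated to falls).
- 5 covariates: estimate 2-3% too large, coverage 94.5-94.9%.
- 9 covariates: 4% too large, variance 4-8% above the 5-covariate model, coverage 94.1-94.8%.
- 19 covariates: 8-10% too large, variance 18-31% above, coverage 93.3-93.6%; type I error under no effect 6.1-7.0%.
- 32 covariates: 16-19% too large, variance 47-75% above, coverage 90.8-92.7%; type I error 7.4-8.5%.

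**The case against.** **The count is a reading.** The protocol does not define the open last item, and it says the drug doses are recorded, not modelled. Residual disability may simply be the Barthel or ADL score, which would lower the count by one or two. Multi-category disease or marital status would raise it. A reader might infer that at least 20, or even 33, parameters are certain to be fitted; the text does not establish that. This part of the objection stands, so the results are given by scenario.

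**Final model form is often left to the analysis plan.** This is true, and the list could be a candidate set. But the article does state a rule, and that rule contains an unbounded term. A later plan could shorten the list only by departing from this text.

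**The harm is modest.** This also stands. At about 20 parameters the coverage loss is one to two percentage points, and it is clear only near 33. With nine covariates the model performs acceptably, so the named items alone are close to tolerable. If there is no effect the estimate is not exaggerated; the only harm is somewhat too many rejections.

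**The main result is not at stake.** A reader might infer that the trial's headline conclusion would be distorted. It would not: the primary analysis is the unadjusted chi-square test, and time to first fall is not among the secondary outcomes listed under Outcome measures.

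**Study group is absent from the list.** A reader might infer that treatment is left out of the model. A list of covariates commonly omits the exposure of interest, so this is at most a wording gap.

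**Conclusion.** The point holds as a defect of a supportive analysis. Followed as written, the model runs at about 5 events per parameter on the named items alone. It falls to about 2.5 or 1.5 if the baseline measures, or those plus the drug classes, are entered.

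If the planned effect is true, the adjusted log hazard ratio is then about 10% (20 parameters) to 16-20% (33) too far from zero. Its variance is roughly 20-30% or 50-75% above that of a five-covariate model, and its 95% interval covers about 93-94.5% or 91-92.5% of the time. If there is no effect, type I error is about 6-7% or 7.5-8.5%.

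These sizes rest on the plan's 22.2% and 40% figures, one parameter per item, proportional hazards and the assumed strength of the covariates, which the protocol does not give. The direction was the same in every setting tried. The change should be made, but the trial's primary conclusion does not depend on it.

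**What to change.** Before the data are analysed, delete the open-ended last item and replace the covariate list. State that the model contains study group, whose hazard ratio is the effect of interest, plus a short set of prognostic variables fixed in advance and already collected. About 5 parameters, and not more than about 9, is a reasonable size; fall history, Berg score, age, sex and MMSE would be one such set. State how each is coded.

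Use the long list only in an exploratory risk-factor model that is not used for the treatment effect.

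The cost is a change of wording, with no new data. The downside is less adjustment for minor covariates, so the retained variables should be the ones expected to predict falls most strongly.
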